## **6.2 Statistical analysis of efficacy and harms**

### **6.2.1 Statistics and data analysis**

Unless otherwise stated further detail in relation to the subsection of 6.2 will be detailed in a statistical analysis plan (SAP), which will be agreed with the Data Management Committee (DMC). No interim analyses are planned, and will be performed only where directed by the DMC. Furthermore, all primary analyses are planned to be on an intention to treat basis with secondary per protocol analysis.

### **6.2.2 Planned recruitment rate**

Recruitment from centres will be based on a staged roll out. The expected rate of recruitment is based on a combination of feasibility data and audit data from the lead centre. The average number of potential participants eligible for the feasibility has been approximately 8.5 per month, recruiting on average five per month. The other centres involved in the trial will all be trauma centres with similar catchment areas to the lead centre. Experience from previous multi-centre trials has shown that recruitment outside of the lead centre tends to occur at a lower rate. As such, a conservative recruitment rate of three participants per month per centre is estimated. We intend to recruit from approximately 18 centres over approximately 17 months.

### **6.2.3 Statistical analysis plan**

All data will be analysed and reported in accordance with the CONSORT statement. Treatment effects will be presented, with appropriate 95% confidence intervals, for both the unadjusted and adjusted analyses. Tests will be two-sided and considered to provide evidence for a significant difference if p-values are less than 0.05 (5% significance level). All analyses will be conducted as intention to treat unless otherwise specified.

#### **6.2.3.1 Summary of baseline data and flow of participants**

Baseline data will be summarised to check comparability between treatment arms, and screening data will be checked to highlight any characteristic differences between those individuals in the study, those ineligible, and those eligible but withholding consent. A CONSORT chart illustrating participant flow throughout the study will also be produced. Standard statistical summaries will be presented for the primary outcome measure (OMAS) and all secondary outcome measures.

#### **6.2.3.2 Primary outcome analysis**

The main analysis will investigate differences in the primary outcome measure, sixteen weeks after randomisation, between the two treatment groups. Unadjusted and adjusted regression analyses will be used to estimate the between group difference. The adjusted analyses will adjust for the stratification variables, baseline scores and any other clinically important variables. More specifically, adjusted mixed-effects modelling will be used where the recruiting centre will be included as a random effect to allow for possible heterogeneity in patient outcomes due to the

recruiting centre. Since individual clinicians will treat only a small number participants enrolled in the trial, we do not expect clinician specific effects to be important in this study and hence will not be modelled. This adjusted mixed-effects linear regression analysis will be reported as the primary analysis, and will be used to assess evidence for differences in outcomes between intervention arms.

#### **6.2.3.3 Secondary outcome analysis**

Descriptive statistics of patient reported outcome measure (PROM) data (i.e. OMAS, MOXFQ, EQ5D and DRI) at each time point will be constructed with between group analyses following the method set out for the primary analysis above. Patterns of recovery will also be explored.

Complications will be summarised with between groups comparisons evaluated using chi-squared tests. Temporal patterns of any complications will be presented graphically and if appropriate, a time-to-event analysis (e.g. Kaplan-Meier survival analysis) will be used to assess the overall risk and risk within individual classes of important complications (e.g. non-union).

### **6.3 Subgroup analyses**

Two pre-specified sub-group analyses will be undertaken to assess whether there is evidence that the intervention effect differs between whether:

- The study participants receives operative or non-operative treatment prior to the study intervention
- The study participants are aged 60 or over at study randomisation

The subgroup analyses will follow the methods described for the primary analysis, with additional interaction terms incorporated into the mixed-effects regression model to assess the level of support for these hypotheses.

The study is not powered to formally test these hypotheses, so they will be reported as exploratory analyses only, and as subsidiary to the analysis reporting the main effects of the intervention in the full study population.

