|--|-------------------------------------------------------------------------------------------------------------------------------------------------------------------------------------------------------------------------------------------------------------------------------------------------------------------------------------------------------------------------------------------------------------------------------------------------------------------------------------------------------------------------------------------------------------------------------------------------------------------------------------------------------------------------------------------------------------------------------------------------------------------------------------------------------------------------------------------------------------------------------------------------------------------------------------------------------------------------------------------------------------------------------------------------------------------------------------------------------------------|--|
|  | 
differences in ankle function assessed using the OMAS scores in operative and non-operative subgroups
 
3. To draw inferences on the observed differences in ankle function assessed using the OMAS scores in those over 50 and those under 50 years of ages subgroups
 
4. To quantify and draw inferences on observed differences between the functional status (MOXFQ) of the trial treatment groups at 16 weeks.
 
5. To quantify and draw inferences on observed differences between health related quality of life (EQ5D-5L) of the trial treatment groups at 6 weeks, 10 weeks, 16 weeks, 24 weeks, 12 months, 18 months and 24 months.
 
6. To quantify and draw inferences on observed differences between the functional status (DRI) of the trial treatment groups at 6 weeks, 10 weeks, 16 weeks, 24 weeks and 24 months.
 
7. To estimate comparative cost-utility of the two trial treatment groups at 6 weeks, 10 weeks, 16 weeks, 24 weeks 12 months, 18 months and 24 months.
 
8. To determine the difference in complications between the trial treatment
 |  |

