In a large study in Norway involving 7600 participants, found that bone mineral density remains stable up until the age of 50 years. After the age of 50, bone mineral density decreased steadily in males, whilst in females there was an initial decline between the ages of 50 and 65, with a further decline in the age groups thereafter [13]. A recent study by Court-Brown [1], assessed over 1000 patients with a fracture. This study confirmed that there is a clear bimodal distribution according to the age of the patient. The crossover of the two peaks of incidence was around 50 years of age. These studies provide strong evidence that patients over the age of 50 become increasingly vulnerable to fragility fractures. Based on this information; and to align with recently published NIHR multi centre RCTs on ankle fracture management [14], we have chosen an age of 50 as the stratification cut-off for this trial.

A final stratification based on operative/non operative presentation will be implemented. This will be used to estimate the extent of the ligamentous injury and the stability of the joint. It will ensure that any effect related to severity of injury is equally distributed amongst the trial arms.

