### Statistical Analysis

Further details of analyses performed as part of this sub-study will be included a more detailed Statistical Analysis Plan (SAP) for this sub-study, which will be reviewed and approved by the AIR Trial Management Group (TMG) prior to commencing data analysis.

The data required for this sub-study will be accessed with the permission of the TMG and this approval will be recorded in the TMG meeting minutes. The trial statistician or nominated delegate will retrieve the data from the AIR online application. This will be transferred to an Excel Spreadsheet and deposited to a file on the AIR Shared folders (M:Drive) on secure University of Warwick servers' access to which is only permitted to authorised trial personnel. All data will be anonymised by trial ID and there will be no identifying patient information on any of the data. At the end of the project, the data will be archived along with the AIR shared folders outlined in the main protocol for the AIR trial.

Data required for this study will be as follows:

1. Patient demographics – Age (y), Age group (49 years and under or 50 years and over), gender, mechanism of injury, side of fracture, weber Classification, number of malleoli involved in fracture, operative or conservative management of fracture.
2. OMAS scores at baseline pre-injury, post-injury, 6 weeks, 10 weeks and 16 weeks.
3. DRI, EQ-5D-5L and M-OXFQ scores for baseline pre-injury, post-injury, 6 weeks, 10 weeks and 16 weeks.
4. The Global Impression of Change Score at the 16 week time point.

There will be no analysis and therefore requirement of data regarding the treatment allocation arm involved in this sub-study. Exact variables required for this sub-study will be outlined in the sub-study SAP.

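### The protocol gives two conflicting age cut-offs for its exploratory age subgroup analysis: 60 in section 6.3, and 50 in secondary objective 3 and the minimisation

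*Protocol*

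**What the plan says.** Section 6.3 announces the subgroup analyses in these terms: "Two pre-specified sub-group analyses will be undertaken to assess whether there is evidence that the intervention effect differs". It lists two. One is operative versus non-operative management. The other is "The study participants are aged 60 or over at study randomisation". Both follow the primary model with interaction terms added. On their standing it says: "The study is not powered to formally test these hypotheses, so they will be reported as exploratory analyses only".

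Elsewhere the protocol uses 50:

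- **Section 2.6.1.** Age is a minimisation factor and serves as a proxy for bone density. After citing work on bone density and fracture incidence, the section says "These studies provide strong evidence that patients over the age of 50 become increasingly vulnerable to fragility fractures" and concludes "we have chosen an age of 50 as the stratification cut-off for this trial".
- **Trial Summary, secondary objective 3.** The age comparison is of "OMAS scores in those over 50 and those under 50 years of ages subgroups".
- **Appendix 2, Statistical Analysis.** The measurement-properties sub-study takes age as "Age group (49 years and under or 50 years and over".

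Section 2.1.2, the list of secondary objectives in the body of the protocol, contains no subgroup objective.

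**The concern.** A subgroup result draws its credibility from having been defined in advance. Here the protocol defines the age subgroup in two incompatible ways. A SAP that follows one must depart from the other, so the SAP alone cannot make the protocol consistent.

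Three things follow if section 6.3 is applied as it stands. Objective 3 has no analysis that answers it. The bone-quality reasoning in section 2.6.1, which is built around 50, is not what the interaction examines, because people aged 50 to 59 are grouped with the younger participants. And the subgroup is not the factor on which minimisation enforces balance between arms.

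**Working it through.** **1. The age thresholds side by side**

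| Place in protocol | Purpose | Cut-off |
|---|---|---|
| 2.6.1 | Minimisation factor, with rationale | 50 |
| Trial Summary, objective 3 | Age subgroups for OMAS | 50 |
| Appendix 2 | Coding of age group in trial data | 49 and under / 50 and over |
| 6.3 | Treatment-by-age interaction | 60 |

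The number 60 is not used as an age threshold anywhere else and has no stated reason. The other subgroup in section 6.3, operative versus non-operative, matches both its minimisation factor and Trial Summary objective 2. Only the age line is out of step.

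**2. What the model would contain**

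Section 6.2.3.2 adjusts the primary model for the stratification variables, so age enters split at 50. Section 6.3 follows that model and adds the interaction. As written, the subgroup model carries age at 50 as a covariate and age at 60 in the interaction. It can be fitted, but the treatment effects it reports are for groups other than those in objective 3.

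**3. Is the sample size affected?**

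Inputs from section 6.1: difference 10, SD 30, two-sided 5%, power 90%, loss 20%.

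- Normal approximation: n per arm = 2 × (1.96 + 1.2816)² × 30² / 10² = 189.1, rounded up to 190, or 380 in total.
- t-test version: 190.1, rounded up to 191 per arm, or 382 in total. This is the protocol's figure.
- After loss: 382 / 0.80 = 477.5, rounded up to 478. This is also the protocol's figure.

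Neither number depends on the age cut-off.

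**4. How many people change group**

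Those aged 50 to 59 are in the older randomisation stratum but the younger group of section 6.3. The share is an assumption.

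| Assumed share aged 50 to 59 | Of 478 randomised | Of 382 evaluable |
|---|---|---|
| 10% | 48 | 38 |
| 15% | 72 | 57 |
| 20% | 96 | 76 |
| 25% | 120 | 96 |

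**5. Precision of the interaction (illustration)**

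With N = 382, SD 30, equal arms and a share f in the older group, SE = 30 × √(4/(N f) + 4/(N(1 − f))). Approximate power for a 10-point interaction is Φ(10/SE − 1.96).

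| f | SE (points) | Power |
|---|---|---|
| 0.5 | 6.14 | 37% |
| 0.4 | 6.27 | 36% |
| 0.3 | 6.70 | 32% |
| 0.2 | 7.67 | 26% |

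The test is weak at any split, as section 6.3 acknowledges. It weakens further if the cut-off at 60 gives a less even split than 50 would. Whether it does depends on the age distribution, which the protocol does not give. The SD of 30 takes no credit for covariate adjustment.

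**The case against.** The best case for leaving this alone is that the analysis is exploratory and subsidiary by the protocol's own words, so nothing that decides the trial turns on it. A subgroup boundary also need not coincide with a minimisation factor. Age is a baseline variable, so treatment is randomised within any age band. Both points stand and they limit the severity. Neither removes the contradiction between section 6.3 and objective 3.

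Several stronger readings are tempting but not supported:

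- *A reader might infer that the 60 cut-off is not pre-specified.* Section 6.3 calls it pre-specified. The accurate statement is that the protocol specifies two.
- *That the comparison at 60 is biased because minimisation used 50.* It is not. What is lost is enforced balance on that split, so the cost is possible chance imbalance.
- *That the cut-off will be chosen after seeing the results.* Section 6.4 has a SAP agreed with the DMC at the start of the study. It is not shown here and may fix one value. The risk is conditional on that document. The fact that participants and clinicians are unblinded does not by itself give the analyst a choice.
- *That 50 is the settled objective throughout.* The age objective is in the Trial Summary only and section 2.1.2 does not repeat it. Appendix 2 shows how age is coded for a sub-study that makes no use of treatment allocation, so it is weak evidence of which interaction was intended.
- *That everyone aged 50 to 59 is declared a fragility case.* Section 2.6.1 describes vulnerability that increases with age and uses 50 as a proxy, not as a diagnosis.

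Two wording points are minor. Objective 3 read literally leaves out a participant aged exactly 50, but Appendix 2 places that age in the older group. Speaking of drawing inferences in the objectives does not conflict with reporting an interaction as exploratory.

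**Conclusion.** The inconsistency is real, and nothing in the protocol reconciles it. Section 6.3 as written does not answer objective 3, classifies those aged 50 to 59 differently from their randomisation stratum, and mixes two age splits in one model. The number reclassified is about 48 to 120 of 478, resting wholly on an assumed 10% to 25% share. It is a count of people, not an estimate of any change in a reported effect.

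The primary analysis, the 382 and 478 sample sizes and the randomised nature of the subgroup comparisons are untouched. This should be rated as an internal inconsistency in an exploratory analysis: worth correcting, and below the level of a defect that must be resolved for the trial's conclusion to stand.

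**What to change.** Before any results by arm are seen:

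1. In section 6.3, define the age subgroup as 50 years or over versus 49 years or under at randomisation, which is the minimisation stratum. Test it as a treatment-by-age-stratum interaction and report it as exploratory.
2. Use the same boundary in Trial Summary objective 3, which also settles where a participant aged exactly 50 belongs.
3. If 60 is intended, state the reason in section 6.3 and amend objective 3 to match. This also removes the contradiction.

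The cost is one line in section 6.3 and one in the Trial Summary, plus a check that the SAP uses the same value. No new data are needed and the sample size does not change.

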### **6.4 Interim analysis and criteria for the premature termination of the trial**

A detailed statistical analysis plan (SAP) will be agreed with the Data Management Committee (DMC) at the start of the study. No interim analyses are planned and interim analyses will be performed only where directed by the DMC, and with the agreement of the TSC.

### **6.5 Procedure to account for missing data**

It seems likely that some data may not be available due to voluntary withdrawal of participants, lack of completion of individual data items or general loss to follow-up. Where possible the reasons for data 'missingness' will be ascertained and reported. The nature and pattern of the missing-ness will be carefully considered, including whether data can be treated as missing completely at random. If judged appropriate, missing data will be imputed using the multiple imputation facilities available in the statistical analysis software.

If imputation is undertaken, the resulting imputed datasets will be analysed, together with appropriate sensitivity analyses. Any imputation methods used for scores and other derived variables will be carefully considered and justified. Reasons for ineligibility, non-compliance, withdrawal or other protocol violations will be stated and any patterns summarised. More formal

analysis, for example using logistic regression with ‘protocol violation’ as a response, may also be appropriate and aid interpretation.

## **6.6 Health Economic Evaluation**

Prospective economic evaluation, conducted from a NHS and personal social services perspective, will be included. The economic evaluation will estimate the difference in the cost of resource inputs between the two intervention groups, enabling costs and consequences to be compared. The methods will adhere to the recommendations of the NICE Reference Case[16].

Primary research methods will be followed to estimate the costs of the treatment options, including resource inputs associated with the plaster materials and braces, supplementary interventions, adverse events and rehabilitation inputs. Broader resource utilisation associated with the ankle injury will be captured through routine health service data collection systems and participant questionnaires administered at each follow up time point.

Unit costs will be estimated from local and national sources in addition to primary research using established accounting methods. Costs will be standardised to current prices where possible. Health-related quality of life will be measured at the time of consent, and all follow time points using the EQ-5D-5L measure. Responses will be used to generate quality-adjusted life years (QALYs) using the UK time-trade-off (TTO) value set recommended by the EuroQol group [17].

Within-trial analysis using bivariate regression of costs and QALYs, with multiple imputation of missing data, will inform a probabilistic assessment of incremental treatment cost-effectiveness from a health service perspective. Missingness mechanisms will be explored and multiple imputation methods will be used where appropriate to avoid biases associated with complete case analysis. Costs and outcomes arising after the first year of the trial will be discounted at 3.5%. Sensitivity analyses will be undertaken to explore uncertainty on the incremental cost-effectiveness ratios and to consider issues of generalisability of the study.

More extensive economic modelling using decision-analytic methods may be considered to extend the target population, time horizon and decision context, drawing on best available information from the literature and stakeholder consultations to supplement the trial data. Parameter uncertainty in the decision-analytic model will be explored using probabilistic sensitivity analysis. Longer term costs and consequences will be discounted to present values using discount rates recommended for health technology appraisal in the UK (current discount rate: 3.5%).

## **7. TRIAL ORGANISATION AND OVERSIGHT**

### **7.1 Sponsor and governance arrangements**

This study will be sponsored by University of Warwick following WCTU’s SOPs.

### **7.2 Ethical approval**

All required ethical approval(s) for the trial will be sought using the Integrated Research Application System. The trial will be conducted in accordance with all relevant regulations.

Before enrolling potential participants into the trial, each trial site must ensure that the local conduct of the trial has the agreement of the relevant NHS Trust Research & Development (R&D) department. Sites will not be permitted to enrol potential participants into the trial until written confirmation of R&D agreement is received by members of the AIR trial team within Warwick Clinical Trials Unit.

All substantial protocol amendments (e.g. changes to eligibility criteria, outcomes, analyses) will be communicated to all relevant parties (e.g. investigators, RECs, NHS Trusts, trial registries) via the TM following WCTU's SOP.

Annual reports will be submitted to the REC within 30 days of the anniversary date on which the favourable opinion was given, and annually until the trial is declared ended. REC will be notified of the end of the trial (whether at planned time or prematurely).

The CI will submit a final report to the required authorities with the results, including any publications within one year of the end of the trial.

This study design has undergone extensive peer review as part of an application process for a NIHR Career Development Fellowship that involved the following:

- Independent: A panel of at least 15 experts reviewed the study and interviewed the CI.
- Expert: Two reviewers with knowledge of the relevant discipline to consider the clinical aspects of the protocol, and/or have the expertise to assess the methodological and statistical aspects of the study also assessed this study protocol outside of the independent panel.

